## Design, subjects and methods

### Overall study design

## A multicentre randomized validation study comparing RDT + clinical diagnosis versus clinical diagnosis alone in the management of uncomplicated malaria.

### Inclusion criteria

## Any patient attending the study site and reporting history of fever within past 48 hours or other symptoms compatible with malaria and giving their informed consent, will be eligible for the study.

### Exclusion criteria

Patient’s refusal to consent will disqualify participation in the study.

### Sample size

## A total of 850 patients will be enrolled. The number of patients needed in each group, based on the assumed reduction in malaria diagnosis of 50% with the addition of RDT to clinical diagnosis, is calculated to 103, at 95% confidence interval and a power of 80%. With 4 study sites this equals 824 patients. Since no active follow up is intended no margin for drop -outs is necessary.

## 4.3.5 Product used

## Paracheck Pf, Cat No. 30301025, M.L.No 635/L, Lot No. 21071, Mfg. Date May 2004, Exp. Date April 2006, Manufactured by Orchid Biomedical Systems, [name].

### Locality

## The study will be conducted in four different Health facilities (HF) in Zanzibar Islands, two in each Unguja and Pemba Islands. The tentative HFs are: Muyuni (Unguja South District), Uzini (Unguja Central), Kinyasini (Pemba, Micheweni District) and Mzambarauni (Pemba, Wete District). Each study site will enrol patients into both study arms.

### Subject recruitment

Subjects will be recruited from patients presenting at the study site fulfilling the criteria for inclusion.

### Duration of study

Each patient will spend approximately 1 hour at the study site. There will be a passive follow up period of a minimum of 14 days after the initial visit, during which any subsequent treatment will be evaluated if the patient is seen/examined at the site again. Depending on the rate of enrollment, which is expected to be 100 patients/week/site, the study will run for approximately 45 days in each site.

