## Medical assessment and blood sampling

- - 1. **Clinical assessment**

The Clinician in charge of each Health facility will instruct all patients to come back for follow up assessment any time if symptoms persist or the condition deteriorates, and always on day 14 (or at any convenient time after day 14). At the time of final follow up patients will receive one insecticide treated net (ITN) free of charge.

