### Serious adverse event definition

A serious adverse event is an adverse event that results in death or is life threatening, an event that requires hospitalization, results in persistent or significant disability or incapacity.

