**6. Budget:**

**Staff allowances**

2 Supervisors x 70,000/- per week x 8 weeks = 1,120,000/-

2 Laboratory technicians x 50,000/- per week x 8 weeks = 800,000/-

4 Prescibers x 50,000/- per week x 8 weeks = 1,600,000/-

4 Community mobilizers x 25,000/- per week x 8 weeks = 800,000/-

1 Data entry clerks x for 4 weeks = 50,000/-

1 Statistician x 150,000/- = 150,000/-

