**Sub Total = 300,000/-**

**Incentive for the patients**

850 ITN x 3,000/- = 2,550,000/-

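### Serious events and revisits after day 0 are captured only if the patient comes back to the site; a death, or an admission of a patient who never returns, has no stated route into the data

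*Protocol*

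**What the plan says.** Five parts of the protocol bear on this.

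- **Duration of study.** Follow-up is passive and lasts at least two weeks. What is assessed in that time depends on attendance: "during which any subsequent treatment will be evaluated if the patient is seen/examined at the site again".
- **Sample size.** "Since no active follow up is intended no margin for drop -outs is necessary".
- **Medical assessment and blood sampling (clinical assessment).** The clinician "will instruct all patients to come back for follow up assessment any time if symptoms persist or the condition deteriorates, and always on day 14". Coming later, when it suits the patient, is also allowed. The net is tied to that visit: "At the time of final follow up patients will receive one insecticide treated net (ITN) free of charge". The Budget provides a net for every enrolled patient: "850 ITN x 3,000/- = 2,550,000".
- **Adverse events.** A serious event is one that "results in death or is life threatening, an event that requires hospitalization", or that leads to lasting disability. The recording section covers events that are encountered. The reporting section undertakes to report every serious event irrespective of causality, with the principal investigator told at once.
- **Study objective.** The primary comparison is the proportion prescribed malaria treatment. Secondary objectives are RDT accuracy and cost benefit, the latter drawing partly on fewer revisits caused by misdiagnosis.

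The section on concomitant drug therapy asks that medication taken during follow-up be recorded where possible. The Budget lists "4 Community mobilizers x 25,000/- per week x 8 weeks = 800,000" but does not describe what the mobilizers do. The Monitoring section says there will be no formal monitoring.

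**The concern.** The undertaking to report all serious events and the means of finding them do not match. Everything learned after day 0 depends on the patient attending the same unit again, yet death and hospitalisation are states that can prevent attendance. The net rewards attendance by the patient; the text does not say that a relative may report for a patient who has died or is in hospital.

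Two things are at stake. The first is the count of serious events in a trial where a test result may lead to no antimalarial being given. The second is the revisit part of the cost-benefit objective: few recorded revisits may mean recovery, or may mean that patients sought care elsewhere. There is no blinding, so return to the site may differ by arm. Data of this kind cannot be recovered by any later analysis, which is why the matter belongs in the protocol.

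**Working it through.** **1. The routes by which an event could reach the data**

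| Situation after day 0 | Stated route |
| --- | --- |
| Symptoms persist, patient returns | Yes: return instruction |
| Recovered, attends on or after day 14 | Yes: day-14 instruction and net |
| Admitted elsewhere, discharged, attends later | Yes: the patient can report it at that visit |
| Admitted or treated elsewhere, never attends | None stated |
| Dies away from the site | None stated |

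Recording concomitant medication helps only for patients who are seen, and it captures drugs rather than visits.

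**2. How many patients could have unknown status**

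The protocol gives no return rate, so non-return q is an assumption. Unknown = 850 × q.

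- q = 10%: 850 × 0.10 = 85
- q = 20%: 850 × 0.20 = 170
- q = 40%: 850 × 0.40 = 340

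**3. What share of serious events could be missed**

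This too is an assumption range. Let r1 be the risk in returners and r2 the risk in non-returners, with no event in a non-returner detected. Then share missed = q·r2 / [(1 − q)·r1 + q·r2]. With r1 = 1%:

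| q | r2 = 1% | r2 = 3% | r2 = 5% |
| --- | --- | --- | --- |
| 10% | 10% | 25% | 36% |
| 20% | 20% | 43% | 56% |
| 30% | 30% | 56% | 68% |

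For example, at q = 20% and r2 = 5%: 0.010 / (0.008 + 0.010) = 56%.

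**4. Unequal return between arms**

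The protocol's 824 patients give 824 / 2 = 412 per arm. With the same assumed true risk of 2% in both arms, and non-return of 10% in one and 30% in the other, the expected observed events are 412 × 0.02 × 0.90 = 7.4 and 412 × 0.02 × 0.70 = 5.8. That difference comes from ascertainment alone.

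**5. What tracing would cost**

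Four sites at the stated 100 patients per week each enrol 400 per week, so 850 / 400 = 2.1 weeks (about 15 days). The day-14 dates fall over an equally short span. At 20% non-return, 170 / 4 mobilizers = 42.5 each, and 42.5 / 2.1 = about 20 per mobilizer per week for roughly two weeks. Slower enrolment would spread this out.

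**The case against.** The strongest reply is that passive follow-up is a declared choice and that the protocol does more than wait. Every patient is told to return on or after day 14, a net is offered for doing so, and nets are budgeted for all 850. A patient admitted elsewhere can report it at that visit. The objectives include no safety comparison. On an assumed event risk of 0.5-1%, the whole trial would see 850 × 0.005 = 4 to 850 × 0.01 = 9 events, too few to compare arms even with complete capture.

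Most of this stands. It limits the point to patients who never come back, and it means the fix would not turn the trial into a safety comparison. It does not supply a route for a death, and it does not square the undertaking to report every serious event with the absence of any means to learn of one. Nor does it answer the cost-benefit objective, which does depend on follow-up.

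Three stronger readings are tempting but unsupported.

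- A reader might infer that non-return will be taken as a safe outcome. No section says so. Since every patient is expected back, absence can be noticed, and how it is counted may be set in an analysis plan that is not shown.
- A reader might infer that all admissions elsewhere are lost. Returning patients can report them.
- A reader might add 14 days to 45, get 59, and set this against the 8 budgeted weeks (56 days). But the 45 days describe how long the study runs at each site, not enrolment alone. At the stated rate, enrolment takes about 15 days, and 15 + 14 = 29 days fits within both limits.

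**Conclusion.** The point holds in a limited form. Capture of serious events and revisits after day 0 depends on voluntary return, and the protocol gives no route for a death or for an admission of a patient who never returns. This conflicts with its own undertaking to report all serious events, and it weakens the revisit part of the cost-benefit objective. The comparison of initial prescriptions, read as prescribing at enrolment, is unaffected, as is RDT accuracy, which uses enrolment blood. The absence of a drop-out margin is no fault for those two.

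The size cannot be derived from the documents. The 85 to 340 patients with unknown status rest on an assumed 10-40% non-return. The shares of missed events rest further on assumed risks and on no event in a non-returner being detected. This is a worthwhile and inexpensive improvement, not a flaw in the main comparison.

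**What to change.** - In the Duration of study and clinical assessment sections, make the existing day-14 contact a status record for every enrolled patient: alive or dead, admitted, treated elsewhere. Allow the patient or a household member to give it, and hand over the net on that report.
- Where feasible, have the budgeted community mobilizers ask after those not seen within a stated short time after day 14.
- In the protocol or the analysis plan, report day-14 status as known or unknown by arm, and do not treat unknown status as event-free or as no revisit.
- Reconcile the statements that follow-up is passive and not active (Sample size, Duration of study) with the instruction that every patient always returns on or after day 14.

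The cost is amendment wording, one CRF entry and some mobilizer time: about 20 patients per mobilizer per week for two weeks at 20% non-return and the stated enrolment rate. The mobilizers' duties are not described, and the text shown does not mention recording home addresses, so the sponsor should confirm that tracing is practicable. The status record is worth having even without it.

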### Randomization

Each study site will alternately use either RDT+CD or CD alone on a weekly basis (*see Annex V)*. During the CD alone week(s) no RDTs will be available at the site. It will be the same clinician who performs both clinical and RDT aided diagnoses, so as to minimize user dependency. The cycle of RDT+CD/CD alone will be timed in such a way that neighboring sites will not be synchronized, so as to insure stable attendance rates.

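### Enrolment target, weekly rate and duration contradict each other, leaving open whether the trial has about 8 or up to 24 alternating site-weeks

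*Protocol*

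**What the plan says.** - **Target** (Protocol, Sample size): "A total of 850 patients will be enrolled". The calculated number per group "is calculated to 103, at 95% confidence interval and a power of 80" percent. It is then multiplied by two groups and four sites: "With 4 study sites this equals 824 patients".
- **Rate and duration** (Protocol, Duration of study): "Depending on the rate of enrollment, which is expected to be 100 patients/week/site, the study will run for approximately 45 days in each site". The same paragraph sets a passive follow-up of at least 14 days.
- **Allocation** (Protocol, Randomization): "Each study site will alternately use either RDT+CD or CD alone on a weekly basis". Neighbouring sites are to be out of phase. Annex V, cited for the schedule, is not in the text available for this review.
- **Arms within sites** (Protocol, Locality): "Each study site will enrol patients into both study arms".
- **Resources** (Protocol, Budget): 850 nets, one per patient at final follow-up; 850 rapid tests; prescribers and supervisors for 8 weeks.

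The available text gives no quota per site, weekly cap, sampling fraction or rule for ending enrolment.

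**The concern.** In most trials a mismatch between accrual rate and duration is a logistic matter. Here the unit of allocation is the site-week, so the length of enrolment decides how many units are allocated.

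A team following the protocol has three ways out. It can stop each site when its share is filled, run the full period and exceed the target, or take only some of the eligible patients. The first leaves very few weeks per arm. The second exceeds the budgeted nets. The third, without a rule, hands selection to unblinded staff who know which arm is running that week.

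Under the first, a local fever outbreak, staff absence or drug stock-out in one of a site's two weeks would look exactly like an effect of the test at that site. This matters because the sample size is applied site by site, and because the objectives include comparing the two sites with prior case-management training against the other two.

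**Working it through.** **Inputs from the protocol:** 850 in total (824 calculated), 4 sites, 2 arms, 103 per group per site, 100 patients per week per site, 45 days, follow-up of at least 14 days, weekly alternation.

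**1. The plan's own total.** 103 × 2 × 4 = 824. This reproduces, and the target of 850 exceeds it by 26. An even split gives 850/4 = 212.5 per site (824/4 = 206). The even split is inferred from this multiplication.

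**2. Time to reach the target at the stated rate.** Days = (N/4)/100 × 7.
- N = 850: 212.5/100 × 7 = 14.9 days
- N = 824: 206/100 × 7 = 14.4 days

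The stated 45 days is about three times as long.

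**3. Patients enrolled at the stated rate and duration.** Total = days/7 × 100 × 4.
- 45 days of enrolment: 6.43 × 400 = 2,571, or 3.0 times 850
- 31 days of enrolment (45 − 14): 4.43 × 400 = 1,771, or 2.1 times 850

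**4. Other readings.**
- Adding 14 days of follow-up to step 2 gives 14.9 + 14 = 28.9 days, not 45.
- Reading 100 per week as the total for all sites gives 850/100 × 7 = 59.5 days, not 45.
- The rate that would fit 850 is 212.5/6.43 = 33 per week per site, or 212.5/4.43 = 48 if follow-up is inside the 45 days.

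No reading reconciles the figures.

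**5. Allocated units.**
- Stopping at the target: 2.1 weeks per site, that is one RDT+CD week, one CD week and about 12 patients in a third. Four sites give about 8 site-weeks. With site and arm in the model, residual df = 8 − 4 − 1 = 3.
- Six full weeks: 4 × 6 = 24 site-weeks, residual df = 24 − 4 − 1 = 19.
- 31 days of enrolment: 4.43 × 4 = about 18 site-weeks.

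**6. Effect on power.** The Sample size section gives no control-arm proportion, so two effects are shown. 50% versus 30% reproduces 103 per group with a continuity correction. 50% versus 25% takes the assumed halving literally from the same starting point (58 per group, 66 with correction). The between-week intraclass correlation (ICC) is an assumption. Site-week counts were simulated as beta-binomial, with 103 patients in each of 8 site-weeks (824) or 34 in each of 24 (816). Site-week proportions were analysed by a linear model with site and arm, two-sided 5%.

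| Comparison | Site-weeks | ICC 0.01 | ICC 0.02 | ICC 0.05 |
|---|---|---|---|---|
| 50% vs 30% | 8 | 79% | 63% | 40% |
| 50% vs 30% | 24 | >99% | 99% | 93% |
| 50% vs 25% | 8 | 93% | 82% | 56% |
| 50% vs 25% | 24 | >99% | >99% | 99% |

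**The case against.** **The duration is only approximate.** It is stated to depend on the enrolment rate. That is fair, but the same sentence gives the rate, and a threefold gap is more than approximation.

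**Arm might be thought confounded with calendar week throughout the trial.** The documents do not support this. Neighbouring sites are out of phase and each island has two sites, so in a given calendar week some sites would use the test while others would not. Complete aliasing of arm with week holds only within a site. What remains in the pooled comparison is the small number of site-weeks and their exposure to site-specific events.

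**Stopping after two weeks is not stated.** This stands. It is one of several ways to resolve the conflict, and it discards the stated duration. Annex V may fix the number of weeks, and the marks in the Annex IV enrolment row are lost in the available text. Neither would remove the conflict between Sample size and Duration of study.

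**The 850 rapid tests might be read as a cap on enrolment.** They are not. Only the intervention arm uses them, so they would serve about 1,700 patients. Only the 850 nets match the target one to one.

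**Power may be adequate anyway.** For 50% versus 25% and an ICC of 0.02 or less, 8 site-weeks still give more than the planned 80%. This stands, but no ICC is given in the protocol, and at 0.05 the figure is 56%.

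**Conclusion.** The contradiction is established by arithmetic on the protocol's own figures: target, rate and duration differ by a factor of about three, or about two if follow-up lies within the 45 days. The consequence is conditional. If sites stop at the target, about 8 site-weeks remain with 3 residual degrees of freedom, and arm is aliased with week within each site, though not with calendar week in the pooled comparison. Power could then lie anywhere from about 40% to 93% over the effects and ICCs examined, against 93% to >99% with 24 site-weeks and almost the same number of patients.

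The power figures rest on an assumed ICC, an assumed control proportion of 50%, an effect common to all sites, and a site-week analysis. The ordering of 8 below 24 site-weeks holds in every case tried. This should be fixed before enrolment; it does not by itself invalidate the pooled comparison.

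**What to change.** 1. Reconcile rate, target and duration in Sample size and Duration of study, and say whether the 45 days include follow-up.
2. Keep 850 and state a fixed number of complete alternating weeks per site, equal between arms. Six weeks, three per arm, gives 850/24 = about 35 patients per site-week.
3. State that a site does not stop early when its total is reached.
4. If attendance exceeds the weekly number, select by a fixed arrival rule that the clinician cannot alter, with the fraction set from each site's actual attendance. A fixed one in three suits about 100 per week. If attendance is nearer 33, it would give 11 per site-week and 11 × 24 = 264 patients in all.

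**Cost:** protocol wording and a simple arrival count, with no more patients, tests or nets. Enrolment cannot finish early. Where attendance is high, some eligible patients would not be enrolled, which changes the recruitment described in Subject recruitment. Six enrolment weeks plus 14 days of follow-up make 42 + 14 = 56 days, which uses all 8 budgeted field weeks and leaves no slack.

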### Blinding procedure

No blinding.

### Randomization

Each study site will alternately use either RDT+CD or CD alone on a weekly basis (*see Annex V)*. During the CD alone week(s) no RDTs will be available at the site. It will be the same clinician who performs both clinical and RDT aided diagnoses, so as to minimize user dependency. The cycle of RDT+CD/CD alone will be timed in such a way that neighboring sites will not be synchronized, so as to insure stable attendance rates.

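### The study is labelled randomised but alternates arms by week, and the week's arm is known before patients are judged eligible and consented

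*Protocol*

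**What the plan says.** Under Overall study design the protocol describes "A multicentre randomized validation study comparing RDT + clinical diagnosis versus clinical diagnosis alone". Under Randomization the method is given as "Each study site will alternately use either RDT+CD or CD alone on a weekly basis", with a reference to Annex V. The same section adds three details:

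- on the supply of tests, "During the CD alone week(s) no RDTs will be available at the site";
- on staffing, a single clinician makes the diagnoses in both arms, with the aim of limiting differences between users;
- on timing, the cycles are set so that "neighboring sites will not be synchronized, so as to insure stable attendance rates".

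The Blinding section states that there is none. Under Inclusion criteria, eligible patients are those "reporting history of fever within past 48 hours or other symptoms compatible with malaria and giving their informed consent", and the only exclusion is refusal of consent. The section on subject information and consent places consent before enrolment. The primary objective compares, between the two cohorts, the proportion prescribed malaria treatment.

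**The concern.** Calling a study randomised tells the reader two things: chance decided which patients fell in which arm, and nobody could foresee the arm when deciding whom to enrol. Fixed weekly alternation, as described, provides neither.

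The primary outcome is a proportion among enrolled patients. If patients with a low suspicion of malaria are enrolled more readily in one kind of week, the proportion treated in that arm changes even if the test has no effect on prescribing. In addition, anything at a site that differs between its RDT weeks and its CD weeks, such as attendance, staffing or local transmission, is attributed to the arm.

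**Working it through.** No stated figure has to be reproduced for this point. It rests on setting the sections side by side, with one piece of arithmetic on the number of weeks.

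**1. Label against method.** Overall study design says randomised. The Randomization section gives alternation by week and mentions no random sequence, random start or concealment. Annex V might contain a random start. Even so, under alternation the first week would determine every later week at that site.

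**2. Is the arm known at enrolment?** The arm is set for the whole week, the tests are physically absent in CD weeks and nothing is blinded. Consent is taken before enrolment, but within a week whose arm is already fixed. Staff knowledge of the arm at screening therefore follows directly from the design. No annex could hide the arm within a week.

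**3. Is there room for judgement at enrolment?** Yes. Besides recent fever, the criteria admit other symptoms thought to fit malaria, and consent is needed. The text requires neither consecutive enrolment nor a record of eligible attenders who were not enrolled.

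**4. Does this reach the primary outcome?** Suppose N patients with treated proportion p would be enrolled in either kind of week, and one arm takes E extra patients with treated proportion q. That arm then shows (Np + Eq)/(N + E). This differs from p whenever q differs from p, and lies below p when q is below p. The documents give no value for p, q or E, so no size can be attached.

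**5. How many weeks separate the arms?** The section on duration expects 100 patients per week per site and about 45 days per site. Sample size gives a total of 850 over four sites.

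- By duration: 45/7 = 6.4 weeks, or about 3 weeks per arm per site.
- By target and rate: 850/4 = 212.5 patients per site, and 212.5/100 = 2.1 weeks, or about 1 week per arm per site.
- Both together: 4 × 100 × 45/7 ≈ 2,570 patients, about three times the 850 planned.

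The number of alternations is therefore unclear. On the shorter reading, arm and week are almost the same thing within a site. On the longer reading, either attendance is lower than expected or only about one patient in three (850/2,570) is taken. The text does not say which.

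**The case against.** The protocol states its mechanism openly and includes real safeguards. Every site enrols into both arms, so differences between sites are balanced. The same clinician works in both arms, by deliberate choice and with a stated reason. Neighbouring sites run out of phase, so a calendar effect they share is spread over both arms. Blood slides are taken from all patients, so a shift in case-mix could show as a difference in slide positivity. The free net at final follow-up gives the same incentive to enrol in both arms. All of this stands, and it narrows the concern to selective enrolment and to week effects specific to one site. It does not remove either. The stated reason for staggering is stable attendance, which suggests that the authors thought attendance might depend on the week's arm.

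A reader might also infer several stronger things that the documents do not support:

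- *That the prescriber screens and consents the patients.* No section says who does. The consent section makes the principal investigator responsible, and the budget lists supervisors and community mobilizers as well as prescribers.
- *That the community knows the schedule.* Nothing says so.
- *That the bias must exaggerate the benefit of the test.* Enrolling more low-suspicion patients in RDT weeks would do that. A clinician who becomes more cautious in CD weeks after seeing negative tests would shrink the difference instead.
- *That the bias amounts to a particular number of percentage points.* The protocol gives neither a control proportion nor any rate of differential enrolment.

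**Conclusion.** The point holds as a matter of design. On the text shown, the study is an alternating-week, quasi-randomised comparison, and the word randomised claims a protection that it does not have. Selective enrolment by arm is possible at the step that sets the primary denominator, and site-specific week effects are confounded with arm. With between about 1 and about 3 weeks per arm per site, there is little opportunity for week effects to average out.

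The conclusion rests on one inference, that staff know the arm when screening, and on the assumption that Annex V adds no more than a random start. Neither the size nor the net direction of any bias can be derived from the documents. The finding is that bias is possible and that the plan does not prevent it, not that it will occur.

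**What to change.** **(a) Label and order.** Either describe the design as alternating-week (quasi-randomised) allocation, or draw the RDT/CD order at random within each two-week block and mirror it at the neighbouring site so that the two stay out of phase. This deals with predictability and with any two-week rhythm. It does not deal with selection within a week, and the second week of each block can still be foreseen. With 6.4 weeks per site there would be only three full blocks, so the gain is modest.

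**(b) Enrolment.** Enrol consecutive attenders who meet the criteria. Ask the fever and symptom question at registration, before the consultation and in the same way in both arms. Log eligible attenders and refusals by week and arm. Compare slide positivity between arms as a check on case-mix, bearing in mind that it cannot separate selection from a true change between weeks. Report the group with fever in the last 48 hours as a sensitivity analysis. It should not replace the primary population, because that would change the patients to whom the result applies.

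**(c) Supportive comparison.** In RDT weeks, record the clinical diagnosis before the RDT is read. This allows a within-patient comparison free of week effects. It is supportive only, because a diagnosis made when a test is about to follow may differ from one made when none is available.

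**Cost.** A registration log, one CRF line and, if the order is randomised, occasionally the same arm two weeks running at a site.
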